### Statistics

The number of evaluable patients (the sample size) is based on Simon’s two stages Mini-max design [26]. This design ensures early study termination if there is insufficient effect. Patients will be evaluated with CT scans every 9 weeks. In randomized trials on second-line therapy, PFS is around 4 months. A tumor control rate less than 10 % after 4 months (at the time of the second evaluation CT scan) is not clinically relevant. Assuming a significance level at 0.05 (α = 0.05) and a power at 80 % (β = 0.20) it can be calculated, that 15 patients should be included in the first part of the study. The enrolment will continue until 15 patients have completed the second CT scan or experienced progressive disease. If none out of the first 15 consecutive patients achieve stable disease at the second CT scan (i.e. after 6 courses of epirubicin), we will reject our hypotheses and close the study after the first stage of accrual. If one or more patients achieve tumor control (partial response or stable disease) at the second scan, an additional 10 patients will be accrued in the second stage. If 5 out of 25 patients achieve tumor control after six courses of therapy, a tumor control rate of 30 % cannot be rejected, and it will be concluded that the treatment is effective enough to continue with future studies.

We will use non-parametric methods for calculation of patient characteristics, side effects and disease control. PFS and OS will be calculated and reported as median survival (Kaplan-Meier method).

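### The stage 1 rule continues on 1 of 15 where the cited minimax design needs 2 of 15, so a drug at the 10 % rate passes the interim look 79 % of the time

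*Protocol article*

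**What the plan says.** The Statistics section of the protocol article states that the sample size "is based on Simon’s two stages Mini-max design" and claims for it that "This design ensures early study termination if there is insufficient effect".

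The design inputs are in the same section:

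- Uninteresting rate: "A tumor control rate less than 10 % after 4 months (at the time of the second evaluation CT scan) is not clinically relevant".
- Target rate: with 5 controlled patients in 25, "a tumor control rate of 30 % cannot be rejected". The Discussion repeats 10 % against 30 % as the statistical basis, there in terms of response rate.
- Error limits: alpha 0.05 and power 80 %.
- Stage 1 size: "15 patients should be included in the first part of the study". Ten more patients follow in stage 2, for a total of 25.

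The interim rule is given in two complementary sentences. The study closes "If none out of the first 15 consecutive patients achieve stable disease at the second CT scan". Otherwise: "If one or more patients achieve tumor control (partial response or stable disease) at the second scan, an additional 10 patients will be accrued". The first sentence names only stable disease and the second names partial response or stable disease. I read both as tumor control, so the rule is to stop at 0 of 15 and continue at 1 or more.

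**The concern.** A Simon design is usually tabulated by its rejection limits r1/n1 and r/n: stop if the count is r1 or fewer, and call the treatment ineffective if the final count is r or fewer. For these inputs the limits are 1/15 and 5/25. The protocol uses 1 and 5 as the counts that are enough to continue and to succeed. This looks like rejection limits read as success thresholds, which moves each boundary by one patient.

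At stage 1 the consequence is a futility look that seldom stops. This look is the only futility check on the cohort that the article describes. The Discussion says the study departs from the usual sequence, in which irinotecan-based therapy often follows failure of oxaliplatin. It also says that earlier studies of epirubicin in unselected patients found less effect than with oxaliplatin- or irinotecan-based options. How often an ineffective drug is taken to the full cohort therefore matters, and readers are told that the design guards against it.

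**Working it through.** **Inputs** (Statistics section): p0 = 0.10, p1 = 0.30, alpha = 0.05 (taken as one-sided, as in Simon's design; the article does not state the side), power = 0.80, n1 = 15, n = 25.

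**Step 1: reproduce the stated sample size.** For a design that continues if the stage 1 count exceeds r1 and succeeds if the total exceeds r,

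P(success | p) = Σ over x from r1+1 to n1 of P(X1 = x) · P(X2 ≥ r + 1 − x), with X1 ~ Bin(n1, p) and X2 ~ Bin(n − n1, p).

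The search runs over (n1, r1, n, r) for the smallest n with P(success | 0.10) ≤ 0.05 and P(success | 0.30) ≥ 0.80, and then for the lowest expected size at p0. The smallest n is 25. The best designs at n = 25 are:

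| r1/n1 | r/n | Type I error | Power | Early stop at 10 % | E[N] at 10 % |
|---|---|---|---|---|---|
| **1/15** | **5/25** | **0.0328** | **0.8017** | **0.549** | **19.51** |
| 2/18 | 5/25 | 0.0326 | 0.8004 | 0.734 | 19.86 |
| 1/16 | 5/25 | 0.0331 | 0.8042 | 0.515 | 20.37 |
| 0/11 | 5/25 | 0.0329 | 0.8022 | 0.314 | 20.61 |

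The protocol's 15 + 10 is reproduced exactly, so the intended design is clear: stop at 0 or 1 of 15, continue at 2 or more, succeed at 6 or more of 25. In this list a stop only at 0 goes with n1 = 11, not 15.

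**Step 2: the interim look at p = 0.10.**

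- As written: P(stop) = 0.9^15 = 0.2059, so P(continue) = 0.7941 and E[N] = 15 + 10 × 0.7941 = 22.9.
- Minimax: P(stop) = 0.9^15 + 15 × 0.1 × 0.9^14 = 0.2059 + 0.3432 = 0.5490, so P(continue) = 0.4510 and E[N] = 15 + 10 × 0.4510 = 19.5.
- Share of the intended stopping probability that is lost: (0.5490 − 0.2059) / 0.5490 = 62.5 %.

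**Step 3: other true control rates.**

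| True rate | P(stop), written rule | P(stop), minimax rule |
|---|---|---|
| 5 % | 0.463 | 0.829 |
| 10 % | 0.206 | 0.549 |
| 25 % | 0.013 | 0.080 |
| 30 % | 0.005 | 0.035 |

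**Step 4: the two boundaries together.**

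| Continue at | Succeed at | Type I error (10 %) | Power (30 %) |
|---|---|---|---|
| ≥ 1 of 15 | ≥ 5 of 25 (as written) | 0.098 | 0.909 |
| ≥ 2 of 15 | ≥ 5 of 25 | 0.093 | 0.898 |
| ≥ 1 of 15 | ≥ 6 of 25 | 0.033 | 0.806 |
| ≥ 2 of 15 | ≥ 6 of 25 (minimax) | 0.033 | 0.802 |

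The stage 1 boundary governs early stopping and hardly moves the error rates. The excess type I error comes from the final cut-off.

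**The case against.** The strongest reply is that the stage 1 boundary does not endanger the final conclusion. With success at 6 of 25, the written interim rule gives type I error 0.033 and power 0.806, both within the stated limits. What is lost is early stopping, on average 22.9 − 19.5 = 3.4 patients at a 10 % rate. That is correct, and it limits the damage to futility control. It does not rescue the text, which names a design it does not follow and claims a property that a 21 % stopping probability does not provide.

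Other points that deserve weight:

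- Individual patients are scanned every 9 weeks and stop at progression, so the interim look is not their only safeguard. It is the only check on enrolling the rest of the cohort.
- The protocol calls rates below 10 % irrelevant, so 10 % is the hardest case in that region. At 5 % the written rule stops 46 % of the time. The minimax rule would stop 83 % of the time, so the gap remains.
- A sponsor may choose a lenient interim look on purpose. The article gives no sign of that.
- The Discussion says 75 % of patients on standard treatment progress by 4 months, which suggests about 25 % control. If that were the uninteresting rate, neither rule would help much: the trial would pass stage 1 with probability 0.987 as written and 0.920 with the minimax boundary. The correction restores the design for 10 % against 30 %. It does not settle whether 10 % is the right reference.

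**Conclusion.** The concern holds. With the protocol's own inputs, the cited minimax design stops at 0 or 1 of 15, while the written rule stops only at 0. At a 10 % control rate, early stopping falls from 54.9 % to 20.6 %, and about four trials in five go on to 25 patients. The claim of early closure for insufficient effect is not supported by the rule as written. No other part of the article repairs it.

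The result is exact. It assumes independent patients with a common control rate, all 15 evaluable at the second scan, a one-sided alpha of 0.05, and the two interim sentences read as referring to the same outcome. The error should be corrected before the interim look, because it is a go/no-go boundary that cannot usefully be changed afterwards.

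**What to change.** Replace the stage 1 rule with: *If 0 or 1 of the first 15 patients have tumor control at the second CT scan, the study closes; if 2 or more do, 10 further patients are accrued.* State its properties: probability of early closure 0.55 and expected sample size 19.5 at a 10 % control rate.

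Correct the final cut-off in the same amendment. With success at 6 or more of 25, the complete design has type I error 0.033 and power 0.802. If only stage 1 is changed and 5 of 25 stays, the type I error is 0.093, nearly twice the stated 0.05.

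If the sponsor prefers to keep the stop at 0 of 15, the protocol should no longer call the design minimax, should drop the claim about early termination, and should state the actual stopping probability of 21 % at a 10 % rate.

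Cost: one sentence for stage 1 and no extra patients. The chance of wrongly closing the study at a true 30 % rate rises from 0.5 % to 3.5 %. Power falls from 80.6 % to 80.2 % with a final count of 6, or from 90.9 % to 89.8 % with the written 5. The Trial status section reports 3 patients included. If accrual is still short of the interim look, the change can be made before any stage 1 decision; the sponsor should confirm this.

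### Calling 5 of 25 a success gives a type I error of about 0.098, not the stated 0.05: both stage boundaries are one patient too low for the Simon minimax design named

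*Protocol article*

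**What the plan says.** All of the following is in the protocol article, Design/methods, Statistics.

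- The sample size "is based on Simon’s two stages Mini-max design".
- Error rates: "Assuming a significance level at 0.05 (α = 0.05) and a power at 80 % (β = 0.20").
- The rate of no interest: "A tumor control rate less than 10 % after 4 months" is described as not clinically relevant. The target rate is 30 %.
- Stage 1: "15 patients should be included in the first part of the study". The study closes if none of the 15 has disease control at the second CT scan. If at least one does, 10 more patients are accrued.
- Final rule: "If 5 out of 25 patients achieve tumor control after six courses of therapy", then "a tumor control rate of 30 % cannot be rejected" and the treatment is judged good enough for further studies.

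The Discussion repeats the 10 % against 30 % contrast as the statistical basis of the protocol, although there it calls the quantity a response rate.

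**The concern.** A Simon design is normally tabulated by its rejection limits: stop if the stage 1 count is at or below r1, and reject the treatment if the final count is at or below r. The tabulated numbers are therefore the largest failing counts. The article attaches continuation to 1 of 15 and success to 5 of 25, which is what results if r1 = 1 and r = 5 are read as the smallest passing counts.

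The reason given for success points the same way. Not rejecting 30 % says only that the data are compatible with the target. It does not show that the rate exceeds 10 %, which is what a significance level of 0.05 is meant to control.

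At stake is the only go/no-go rule that the article states. If the limit is too low, an inactive treatment goes forward more often than the plan declares.

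**Working it through.** **Inputs** (Statistics section): p0 = 0.10, p1 = 0.30, alpha = 0.05, power = 0.80, n1 = 15, n = 25. Rule as written: continue if X1 ≥ 1, success if the total is ≥ 5.

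**Step 1. Reproduce the plan's sizes.** Take all two-stage designs with type I error ≤ 0.05 at p0 and power ≥ 0.80 at p1. The smallest n is 25, and at that n the lowest expected sample size under p0 belongs to r1/n1 = 1/15, r/n = 5/25. Its type I error is 0.0328, its power 0.802 and its expected n at 10 % is 19.5. The 15 and 25 match exactly. The limits in this design are: stop on ≤ 1 of 15, reject the treatment on ≤ 5 of 25, success on ≥ 6.

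**Step 2. Type I error of the rule as written.**

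P(success | p) = Σ over x ≥ 1 of P(X1 = x) · P(X2 ≥ 5 − x), with X1 ~ Bin(15, p) and X2 ~ Bin(10, p).

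At p = 0.10:

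| x in stage 1 | P(X1 = x) | P(X2 ≥ 5 − x) | product |
|---|---|---|---|
| 1 | 0.3432 | 0.0128 | 0.0044 |
| 2 | 0.2669 | 0.0702 | 0.0187 |
| 3 | 0.1285 | 0.2639 | 0.0339 |
| 4 | 0.0428 | 0.6513 | 0.0279 |
| ≥ 5 | 0.0127 | 1 | 0.0127 |

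The sum is 0.0977 (from unrounded terms). The same formula at p = 0.30 gives power 0.909.

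**Step 3. All four combinations of boundaries.**

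| Stage 1 stop | Success | Type I error at 10 % | Power at 30 % |
|---|---|---|---|
| 0 of 15 (as written) | ≥ 5 of 25 (as written) | 0.0977 | 0.909 |
| ≤ 1 of 15 | ≥ 5 of 25 | 0.0933 | 0.898 |
| 0 of 15 | ≥ 6 of 25 | 0.0334 | 0.806 |
| ≤ 1 of 15 (minimax) | ≥ 6 of 25 (minimax) | 0.0328 | 0.802 |

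The final limit drives the type I error. Correcting stage 1 alone leaves it at 0.093.

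**Step 4. What the stage 1 limit does change.** Probability of stopping early at a true 10 %:

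- stop on 0: 0.9^15 = 0.206
- stop on 0 or 1: 0.9^15 + 15 · 0.1 · 0.9^14 = 0.206 + 0.343 = 0.549

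Expected n at 10 % is 15 + 10 · (1 − 0.206) = 22.9 as written, against 15 + 10 · (1 − 0.549) = 19.5.

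**Step 5. What 5 of 25 shows.** Ignoring the interim look, P(X ≥ 5 | n = 25, p = 0.10) = 0.098, and the exact 95 % confidence interval for 5/25 is 6.8 % to 40.7 %. It includes 10 %. For 6 of 25 the one-sided p-value is 0.033.

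**The case against.** The strongest defence is one of context. This is a single-arm proof-of-concept study whose named primary endpoint is progression-free survival, reported as a Kaplan-Meier median. The boundary leads only to further studies, and some phase II designers would accept a type I error of 0.10. That stands as a limit on the consequence: a false positive costs another study, not a change in practice. It does not make the stated 0.05 true.

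One could also say that the rate of no interest lies below 10 %, not at it. With success at ≥ 5 of 25, the error is 0.045 at p0 = 8 % and 0.068 at 9 %, so the null rate would have to be about 8 %. No such figure appears, and the sizes fit 10 % exactly.

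Three stronger readings are tempting but unsupported:

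- *That the sample size is wrong.* It is not; 15 and 25 are right for the stated inputs.
- *That changing only the final sentence restores the minimax design and its 80.2 % power.* It does not. With stage 1 left at stopping on 0 of 15, power is 80.6 %, and the limits still differ from those of the design named.
- *That the plan's reasoning would equally admit 4 of 25.* P(X ≤ 4 | 0.30) = 0.090, so 30 % is not rejected at a 5 % level but is rejected at a 20 % level. The latter would also reject it at 5 of 25 (P = 0.193). The article gives no level for this statement, so the example settles nothing.

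**Conclusion.** The point holds. The decision rule contradicts the error rate stated beside it: "Assuming a significance level at 0.05" is not met, because a positive conclusion at 5 of 25 carries a type I error of 0.098. The stage 1 limit has the same one-patient slip. It hardly affects the type I error, but it cuts early stopping under an inactive treatment from 0.549 to 0.206.

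This rests on p0 = 10 % and p1 = 30 % for tumor control, on a one-sided test as is usual for a Simon design (the article does not state sidedness; a two-sided 0.05 would make the excess larger), and on reading 5 of 25 as 5 or more. The last matters little, since the positive conclusion is attached to 5 itself. That the slip came from misreading tabulated limits is an inference from the pattern; the finding does not depend on it.

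**What to change.** Amend the Statistics section as follows.

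1. **Final rule.** With 6 or more of 25 patients showing tumor control, a rate of 10 % is rejected and the treatment is considered worth further study; 5 or fewer is a negative result.
2. **Stage 1.** Either set it to the minimax limit (stop on 0 or 1 of 15), or keep stopping on 0 of 15 and say that this departs from the minimax limit.
3. **Operating figures.** Quote those of the rule chosen: alpha 0.033 and power 80.6 % with stopping on 0 of 15; alpha 0.033 and power 80.2 % with stopping on 0 or 1.
4. **Justification.** Replace the statement that 30 % cannot be rejected with one that 10 % is rejected.

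If the sponsor prefers to keep 5 of 25, alpha should be restated as about 0.10 and power as 0.91.

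Cost: a short amendment and no extra patients. The success bar rises by one patient, and power falls from 0.909 to about 0.80, which is the power that the plan states. Trial status reports 3 patients on treatment, so at that point the change could precede any stage 1 result.

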## Methods

The *TOP2A* FISH pharmDx™ Kit (Dako, Glostrup, Denmark) will be used according to the manufacturer’s instructions, as previously reported [23]. For every patient tumor sample, *TOP2A* and CEN-17 signals will be counted in 60 non-overlapping malignant cells, and a *TOP2A*/CEN-17 ratio will be calculated as the total counted number of *TOP2A* signals divided by the total counted number of CEN-17 signals. *TOP2A* FISH analysis will be performed on archived FFPE tumor tissues obtained from either the primary tumor (at time of diagnosis or obtained from the surgical resection specimen) or from a metastatic lesion (biopsy or resection specimen).

## Discussion

The number of treatment options in patients with mCRC is still very limited. Response rates decrease dramatically with time, while the patients proceed in the treatment lines. New and non-cross resistant treatment options are urgently needed, and biomarkers predictive of response to chemotherapeutic treatments are totally lacking. Studies on breast cancer patients indicate that amplification and possibly deletion of *TOP2A* is predictive of response to epirubicin [20, 21]. Data on *TOP2A* aberrations in CRC are sparse, with reported *TOP2A* amplification rates ranging from 2.2 to 46.6 % in studies using different analytical methods [23, 27, 28]. In a study of the frequency of *TOP2A* gene aberrations in CRC tissue, we found that a total of 10.5 % of the patients had a *TOP2A*/CEN-17 ratio ≥ 1.5, which is compatible with *TOP2A* amplification [23]. Previous studies have investigated the effect of epirubicin in the entire unselected group of patients with mCRC, but found that this treatment had lower impact than oxaliplatin- or irinotecan-based treatment options [18, 29–31]. Taken together, those data led to the hypothesis that re-purposing epirubicin to patients with mCRC and *TOP2A* gene amplification may represent a valid treatment offer to a subset of mCRC patients. Hence, the aim of this clinical study is to take a further step towards personalized mCRC treatment. If epirubicin should prove to be effective in patients with increased *TOP2A* gene copy numbers, this may lead to a novel personalized treatment option for patients with mCRC.

This study differs from the standard treatment strategy for mCRC, where the patients often will be offered irinotecan-based therapy after failure to oxaliplatin-based therapy or vice versa. Median PFS of this standard treatment is approximately 2 months, and 75 % of the patients will experience progressive disease after 4 months of treatment [10]. In the present phase II protocol with pre-selected patients, we expect that 30 % will have objective response after the first 4 months of treatment, thereby achieving an increased median PFS. All patients will be evaluated every 9 weeks, enabling a quick change in treatment strategy if a patient experiences disease progression during epirubicin treatment [32, 33]. Carefully planned and closely monitored “window of opportunity” phase II studies are feasible and ethically acceptable in mCRC patients, and may have the advantage to determine potential efficacy of novel agents without placing the patients at risk. In the present study, close monitoring of efficacy every 9 weeks will ensure that this novel treatment line with epirubicin will be offered without further delay in case of progression during epirubicin treatment, with respect to any future treatment option.

The statistical basis for the protocol is based on the fact that we expect a response rate of 30 % in this sub-population of patients with *TOP2A* aberrations, which is significantly better than the typical second line treatment these patients will be offered, which usually has response rates of 10 %. In conclusion, if the objectives of this study protocol are met, the expected 10 % of mCRC patients with a TOP2A/CEN-17 ratio ≥ 1.5 will be offered an extra line of effective treatment, which may lead to an overall improved survival in this subgroup of mCRC patients.

## Trial status

A total of 120 patients have been screened for *TOP2A* levels and we have found 14 patients (12 %) to have a *TOP2A*/CEN-17 ratio ≥ 1.5 in primary tumor, a metastatic lesion or both. To date 3 patients have been included and initiated treatment with epirubicin.
